#### Spatial grid navigation

On each trial, participants see an empty grid made up of nine squares, subtending 10° visual angle for 1600 ms. A start square, highlighted in red, is displayed for 2500 ms, and participants are told to hold the position of the start square in memory. A sequence of five screens are displayed (1500 ms + 100 ms blank ISI) showing sequences of two, three or four arrows (subtending 4°), interspersed with grey hash marks as placeholders. The arrows indicate movement of the red starting square by one space in any of the four cardinal directions (up, down, left, right), restricted within the boundaries of the grid. No movements are made to the placeholders. Participants must track the position of the red square based on the observed sequence, in their minds eye. At the end of the sequence, a test grid is presented with a target square highlighted in blue. Participants must decide if the position of the blue test square is consistent with the final position of the presented sequence (50:50 same-different). Participants make a vocal ‘same’ or ‘different’ response whilst the test grid is on the screen (3000 ms).

#### Control group A: sequential subtraction

A minimum of 10 (up to maximum of 20) participants will be enrolled into this arm of the study, dependent on recruitment success. The trial sequence for this task is identical to the spatial grid navigation task with a few modifications. The start square is replaced with a number highlighted in red. The arrows in the sequence were replaced with the numbers 1–9, which had to be sequentially subtracted from the start number before deciding whether the test number, presented in blue, was the same or different as the final total in the sequence. Sequences varied in length from two to four numbers, plus between one and three placeholders.

#### Control group B: spatial memory

A minimum of 10 (up to maximum of 20) participants will be enrolled into this arm of the study, dependent on recruitment success. This task contains no spatial sequencing component and will provide a pure baseline for the present study. In this task, participants see a start square, highlighted in red, and are told to hold its position in memory for a duration of two to four successive placeholders (1600 ms ea.) before a test grid appears with a square highlighted in blue. Participants are instructed to verbally report whether the test grid is in the ‘same’ or ‘different’ position to the start grid.


**Table 1 Tab1:**
[figure not shown]
Schedule of enrolment, interventions and assessments

^a^Delivered twice per session, pre and post intervention tasks. Finger tapping is always administered before movement kinematics

**The time between sessions will be variable, in keeping with participants’ schedules and other commitments

### Sample size

The target sample size for this study is between 40 and 60 participants. On the basis of our previous work, we estimate an attrition rate of 20%. Participants who are unable to complete the study or withdraw for any reason will be replaced. The target sample estimate is based on a maximum sample that we can reasonably expect to obtain over a 9–12-month active recruitment period, given the population and both clinical and research resources available.

### Statistical methods

Summary statistics for demographic and background information will be reported for all participants in each of the three groups. Presented figures will endeavour to provide an overview of individual data points as well as measures of central tendency, variance and 95% confidence limits. Exploratory analyses exploring the relationships between participant characteristics, intervention intensity and primary/secondary outcomes will be conducted to inform future work. With sufficient participants, mixed effects analyses will be applied to secondary outcome measures and intervention data, to identify potential patterns of effects, which will enable us to characterise both within- and between-subject variances. The analyses are primarily designed to support descriptive analysis of data and inform future power calculations for analyses of this type. Interpretation of patterns of data will be cautionary and based upon estimates of confidence to guide future hypothesis testing.

### Data handling and storage

Identifying participant information will be stored in a password-protected database on an external, encrypted hard disc. Additionally, the IDgenerator [34] software creates layered ID numbers linking an ID paired with identifying information in a separate password-protected database to an ID number associated with study data using a third, temporary ID. At the close of the study, this link will be erased and identifying information will be destroyed. Over the course of the study, electronic data will be stored on a password-protected laptop with an active firewall and anti-virus. Regular backups of electronic data will be made on an encrypted external hard drive and automatically uploaded to a protected web server. During transport between sites, anonymised participant packs and the laptop will be locked in a file box, in a locked car boot. Consent forms and completed participant packs will be stored in a locked file cabinet in a locked office at Bangor University. All data will be kept for 10 years following final access.

### Auditing

The project will be subject to independent auditing by Betsi Cadwaladr University Health Board as the funding body and by Bangor University as the sponsor. The trial team will meet quarterly to discuss the trial progress and/or modifications. Regular updates will be sent out to all members of the team, as well as the clinical studies officer assisting with recruitment.

### Harms

This is non-Clinical Trial of an Investigational Medicinal Product (non-CTIMP) and as such poses minimal risk to participants, and it is not necessary to institute a formal data management committee. We do not anticipate any adverse or serious adverse events will arise during the course of the study. Reporting of such events will be carried out in accordance with NHS policies. Worsening symptoms of PD, hospital stays for elective treatment for pre-existing medical conditions or death resulting from PD will not be reported as SAEs.

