We have previously examined this possibility in a local NHS-funded pilot study (BCUHB 05/WNo03/27; unpublished). Sixteen people with early-stage (H&Y 1/2) PD, tested during the ‘ON’ phase, with age-matched controls, completed a visuospatial ‘intervention’ task of mental grid navigation and a control task of sequence memory, in two separate sessions, a week apart. Immediately before and after the two tasks, we obtained precise measures of movement onset delay and velocity with a simple reaching task completed on a touch-sensitive screen. There were no significant changes in movement onset time, or velocity following either tasks, in the control group. However, the people with PD showed a reduction in motor performance in the simple reaching task (slower mean onset and velocity) following the control task, but an enhancement of motor performance following the visuospatial task (faster mean onset and velocity). This pattern was found in 12/16 (75%) participants. These data provide some evidence that the performance of cognitive tasks that involve visuospatial processing—even after a single 20-min session—can enhance resilience to motor slowing and improve motor function, reducing hypokinesia and bradykinesia. As a form of hypothesis-driven cognitive intervention for motor dysfunction, this approach could potentially have significant clinical benefits for people with PD. If effective, the approach could form the basis of a low-cost, non-pharmacological, treatment that could be made accessible to large numbers of people in the form of a portable software/web-based programme of exercises for home use.

Before the intervention can be considered for a large-scale clinical trial, we first need to better understand the size and robustness of effects in larger samples and assess its clinical significance—whether the intervention leads to levels of improvement in movement onset and velocity that are of benefit to people with PD and whether the benefits to motor function extend to other aspects of the illness such as reduced rigidity and increased motor fluency.

This pilot trial will examine these issues and further our understanding of the potential of this novel approach to the treatment of motor dysfunction in PD. This research will form a vital step in evaluating the clinical significance of the approach, its suitability as an intervention for people with PD and the feasibility of a future large-scale clinical trial.

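### The SAE exemption for worsening Parkinson's disease has no relatedness condition, although motor function is what the tasks are meant to change, and early leavers have no final UPDRS-III

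*Protocol article*

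**What the plan says.** The Harms section classes the study as minimal risk and expects no adverse events. It says of oversight that "it is not necessary to institute a formal data management committee" and of any events that do occur that "Reporting of such events will be carried out in accordance with NHS policies". It then makes an exception: "Worsening symptoms of PD, hospital stays for elective treatment for pre-existing medical conditions or death resulting from PD will not be reported as SAEs". The exception for worsening and for PD death carries no condition on relatedness to the tasks.

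Three other parts of the article bear on this rule.

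- **Earlier pilot (introduction).** Of performance after the comparison task, the article reports that "the people with PD showed a reduction in motor performance in the simple reaching task (slower mean onset and velocity) following the control task". Performance improved after the visuospatial task. The combined pattern was seen in 12 of 16 people with PD.
- **Sample size.** "The target sample size for this study is between 40 and 60 participants", with attrition put at 20%. "Participants who are unable to complete the study or withdraw for any reason will be replaced".
- **Primary clinical outcome measure and Procedure.** UPDRS-III is taken twice, at the start of session 1 and the end of session 5. Finger tapping and movement kinematics are taken before and after the task in every session.

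**The concern.** Exempting expected disease events from SAE reporting is ordinary practice, and it does little harm when the intervention is not aimed at those events. Here it is aimed at them. The Aims and the Secondary objective say that the grid navigation task is meant to act on motor slowing and motor fatigue, with two other cognitive tasks as comparators. An effect in the unwanted direction would appear as worsening PD motor symptoms, which is the category exempted whatever its cause.

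The rule on leavers adds to this. If a participant worsens seriously and stops, the exemption removes the SAE report, the schedule yields no second UPDRS-III, and a replacement fills the place. If this happened unequally between arms, the SAE record and the UPDRS-III change would not show it. The pilot is meant to inform a decision on a larger trial, so a harms summary that is clean partly by rule would be a poor basis for that decision.

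**Working it through.** The article gives no computed figure on harms, so there is nothing to reproduce. The check has two parts: following a participant through the stated rules, and sizing the group of leavers.

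**1. A participant who worsens and stops after session 3, on the published text**

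| Source of information | Rule and section | What remains |
|---|---|---|
| SAE report | PD worsening is exempt, related or not (Harms) | None, even if serious |
| UPDRS-III | Start of session 1 and end of session 5 only (Primary clinical outcome measure; Procedure) | Baseline only; no change score |
| Tapping and kinematics | Before and after the task in every session (Secondary patient-centered outcome measures; Procedure) | Three before-and-after pairs |
| Place in the sample | Leavers are replaced (Sample size); the recruitment criterion counts those who finish five sessions (Recruitment) | Taken by another participant |

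The loss is therefore specific. The SAE report and the final UPDRS-III are missing, and so is any motor measurement after the last attended session. The session-level motor data are kept.

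**2. Is motor worsening foreseeable?**

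The introduction reports slower mean onset and velocity in people with PD straight after one session of a sequence memory task. The comparators in this trial are sequential subtraction and spatial memory, given over five sessions. The pilot result makes a task-related change in the unwanted direction plausible. It does not show that these comparators produce one.

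**3. Expected number of leavers, any cause**

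Inputs: target 40 to 60, attrition d = 0.20 (Sample size); arms of 20, 10 and 10 for the first 40, aiming for 20 per arm (Randomisation).

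If the target means completers, enrolled = n / (1 − d) and leavers = enrolled − n:

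- n = 40: 40 / 0.8 = 50 enrolled, 10 leavers.
- n = 60: 60 / 0.8 = 75 enrolled, 15 leavers.
- Arm of 20: 20 / 0.8 = 25 enrolled, 5 leavers.
- Arm of 10: 10 / 0.8 = 12.5, rounded up to 13 enrolled, 3 leavers.

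If the target means enrolled, leavers = n × d:

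- 40 × 0.2 = 8.
- 60 × 0.2 = 12.

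These are all-cause counts. The article does not divide them by reason, so they bound the group in which a worsening could go unseen and do not estimate how many worsen.

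**The case against.** **The exemption covers SAE reporting, not all recording.** A reader might infer that worsening PD is not recorded at all. The article does not say so. It excludes these events from being reported as SAEs, sends adverse events to NHS policies that are not shown, and says the team will attend to difficulties participants meet. Brief slowing after a task would not obviously be serious in any case. This stands, and it confines the point to serious worsening and to what the harms summary will show.

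**Leavers are not lost to motor measurement.** A reader might infer that worsening is measured only in those who finish. For tapping and kinematics that is wrong, as the table above shows. It is right only for the UPDRS-III change.

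**The pilot signal is thin.** It was immediate, followed a different task, and concerned reaching speed. The Intervention section treats spatial memory as a neutral baseline and allows that subtraction may help. A reader might infer that the comparators are known to worsen PD, or that the tasks are linked to PD deaths. Nothing in the article supports either. Deaths matter here only because the same unconditional sentence exempts them.

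**The leaver counts do not measure the defect.** This is correct. A reader might take 10 to 15 as the number lost through worsening, but the article attributes no withdrawal to it.

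**The full protocol may say more.** An exit assessment, an event log or a withdrawal form could stand in version 4.0, and the article commits to CONSORT reporting. For those details the objection holds, and their absence from the article is not criticised. It does not reach the exemption, which the article states as a rule.

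**Conclusion.** The point holds in a limited form. The published rule exempts PD worsening and PD death from SAE reporting whether or not the event might be related to the tasks, in a trial whose tasks are meant to change PD motor function. Together with replacement of leavers and a single post-baseline UPDRS-III at the end of session 5, it leaves a route by which serious worsening could be absent from both the SAE record and the primary clinical outcome. The effect on the harms summary cannot be quantified from the article.

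This assumes that the schedule in the article is complete, with no early-exit UPDRS-III, and that NHS policies do not override the stated exemption. The change is worth making because it is cheap and protects the safety information passed to a larger trial. The point is not evidence that any participant has been or will be harmed.

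**What to change.** 1. **Qualify the exemption.** Limit it to events judged unrelated to the study tasks, or to expedited reporting only.
2. **Log and tabulate.** Record PD worsening, hospital stays and deaths that come to the team's attention during participation, with date and judged relation to the tasks. Tabulate all of them by arm whatever the judgement, because the researcher who delivers the tasks knows the allocation.
3. **Account for leavers.** Tabulate withdrawal reasons by arm, including participants who were replaced.
4. **Optional.** Give the number of completers per arm whose UPDRS-III rose by 5 points or more, the size of change named in the Secondary objective. This covers completers only and does not substitute for item 3.

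The cost is a revised sentence in the Harms section, a short event and withdrawal log, a longer harms listing, and a relatedness judgement for each logged event. Because the log is limited to what reaches the team during participation, it requires no extra visits or follow-up of people who have left.

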### Protocol version

This paper is based on protocol version 4.0 (30/01/2018). Any amendments will be communicated with the study team and addressed in a final published manuscript once results are known.

### Dissemination

The data will be presented at national and international conferences and published in peer-reviewed journals. The headline results of the study will be shared with participants at the close of the study and made available to the wider public through national bodies (e.g. Parkinson’s Disease UK).

## Discussion

The protocol described is hypothesis-driven, founded on previous pilot data from an independent group of people with PD and underpinned by a considerable body of work which supports the link between activation of the SMA and visuospatial processing. Our previous data demonstrated a significant improvement in measures of movement kinematics and motor fatigue following a single administration of the spatial navigation task. However, the question remains whether repeated exposure to the same intervention would result in a cumulative improvement or support maintenance of current functioning, providing the basis for the future development of this non-pharmacological cognitive intervention. If we observe the expected effects, we would utilise the data for a formal power calculation to inform a large-scale RCT. The longer-term view is to develop an evidence-based, online or app-based platform that could be accessed by people in their own homes alongside other pharmacological or physical treatments to support maintenance of motor slowing and motor fatigue symptoms. An app-based or online portal would enable automatic allocation to intervention condition and complete double blinding of the intervention conditions and concealment during data analysis stage.

As it currently stands, the study protocol is restricted to early-middle disease stage for adults with good cognitive function. This feasibility trial will enable us to refine procedures and task instructions to maximise accessibility and engagement with the tasks, which can be further developed for application to the broadest possible sample. In the face of favourable results, future directions should include longer term follow-up and tracking of motor decline in people with PD. The results from this study will provide valuable insight into the feasibility of cognitive interventions of this type and generate/refine hypotheses for future studies.

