## Abstract

**Background:**

Parkinson’s disease (PD) is a chronic, neurodegenerative disorder affecting over 137,000 people in the UK and an estimated five million people worldwide. Treatment typically involves long-term dopaminergic therapy, which improves motor symptoms, but is associated with dose-limiting side effects. Developing effective complementary, non-pharmacological interventions is of considerable importance. This paper presents the protocol for a three-arm pilot study to test the implementation of computer-based cognitive training that aims to produce improvements or maintenance of motor slower and motor fatigue symptoms in people with PD. The primary objective is to assess recruitment success and usability of external data capture devices during the intervention. The secondary objectives are to obtain estimates of variance and effect size for changes in primary and secondary outcome measures to inform sample size calculations and study design for a larger scale trial.

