### Secondary objective

Estimation of variance and effect sizes to inform power calculations for larger scale RCTs for primary and secondary outcome measures:A clinically relevant change in UPDRS-III motor examination scores of at least 5 points from pre to post measurements in response to spatial grid navigation training relative to the other control tasks.Improvement in movement kinematic response times over the course of the five intervention sessions in response to spatial grid navigation training relative to the other control tasks.Improvement in motor fatigue measures over the course of the five intervention sessions in response to spatial grid navigation training relative to the other control tasks.

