### Primary clinical outcome measures

The change in the motor examination score from the Unified Parkinson’s Disease Rating Scale - III (UPDRS - III; [33]) from Session 1 to Session 5.

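### Using the pilot's effect size to plan the RCT, and only when the effect looks as hoped, is likely to leave the RCT underpowered, often severely

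*Protocol article*

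**What the plan says.** The Abstract (Background) says the secondary objectives are to "obtain estimates of variance and effect size for changes in primary and secondary outcome measures to inform sample size calculations". The Secondary objective section repeats this: "Estimation of variance and effect sizes to inform power calculations for larger scale RCTs for primary and secondary outcome measures". Effect size is therefore a named input alongside variance.

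The Discussion attaches a condition: "If we observe the expected effects, we would utilise the data for a formal power calculation to inform a large-scale RCT". The expected effects are not defined there. The only numerical benchmark is in the Secondary objective section: "A clinically relevant change in UPDRS-III motor examination scores of at least 5 points from pre to post measurements", which that sentence then sets against the control tasks.

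Under Sample size, "The target sample size for this study is between 40 and 60 participants", a figure "based on a maximum sample that we can reasonably expect to obtain". It rests on recruitment capacity, not on precision. Randomisation fixes 20/10/10 for the first 40 participants and aims for 20/20/20 if recruitment allows.

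Two other sections bear on the point. Primary objective bases feasibility for the RCT on recruitment/retention and device usability. Statistical methods describes the analyses as mainly descriptive and promises cautious interpretation guided by confidence estimates.

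**The concern.** Two separate problems combine. First, an effect size from arms of 10 to 20 is too imprecise to serve as a planning value. Second, carrying it forward only when it meets expectations keeps the overestimates and drops the underestimates, so the retained values are too high on average. Required sample size varies with the inverse square of the effect, so a modest overestimate shrinks the RCT considerably.

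Supplying inputs for the RCT's power calculation is this pilot's stated secondary objective. An RCT sized this way would have a nominal power that it does not really have. The condition also brings an efficacy result into a progression decision that Primary objective rests on feasibility alone.

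**Working it through.** The protocol states no power-based sample size, so there is no figure of its own to reproduce.

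**Inputs from the protocol.** Arms of 20/10/10 at 40 participants and 20/20/20 at 60 (Randomisation); a minimum of 30 completers (Recruitment); a 5-point UPDRS-III benchmark (Secondary objective).

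**Assumptions, because the protocol gives none.** RCT with two equal arms, two-sided alpha 0.05 and 80% power; true d of 0.3, 0.5 or 0.8; go rule from any positive estimate to d ≥ 0.5; UPDRS-III change SD of 5 to 12 points.

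**1. Precision of the pilot effect.** Near d = 0, SE(d) = √(1/n1 + 1/n2).
- 20 v 10: √(0.05 + 0.10) = 0.387. With t = 2.026 (37 df) the 95% half-width is 0.78 SD.
- 20 v 20: √(0.05 + 0.05) = 0.316, half-width 0.64 SD.
- An observed d of 0.5 at 20 v 10 has SE √(0.15 + 0.25/60) = 0.393, so the 95% CI is 0.5 ± 1.96 × 0.393 = −0.27 to 1.27.
- On UPDRS-III the half-width equals the whole 5 points once the SD reaches 5/0.78 = 6.4 (20 v 10) or 5/0.64 = 7.8 (20 v 20).

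**2. How an overestimate reaches the RCT.** n per arm = 2(1.96 + 0.842)²/d² = 15.70/d². If the pilot shows d = 0.7, n = 15.70/0.49 = 32.04, rounded up to 33. True power is about Φ(d√(n/2) − 1.96). At a true d of 0.5 this is Φ(2.03 − 1.96) = 53%; at a true d of 0.3 it is Φ(1.22 − 1.96) = 23%.

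**3. Averaging over pilots.** Simulation with 200,000 pilots per scenario and normal outcomes, SD estimated on 37 df (57 df for 20 v 40, which is grid navigation against both controls pooled at 60 participants). Pilots meeting the go rule are kept, the RCT is sized by the formula above, and true power is averaged.

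| True d | Go rule | 20 v 10 | 20 v 20 | 20 v 40 |
|---|---|---|---|---|
| 0.3 | any positive | 58% | 62% | 65% |
| 0.3 | d ≥ 0.5 | 23% | 25% | 26% |
| 0.5 | any positive | 68% | 71% | 73% |
| 0.5 | d ≥ 0.5 | 46% | 50% | 53% |
| 0.8 | any positive | 75% | 76% | 77% |
| 0.8 | d ≥ 0.5 | 68% | 71% | 74% |

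An intermediate rule of d ≥ 0.3 gives 36–43% at a true d of 0.3 and 59–66% at 0.5. The selection bias is visible in the retained estimates: at 20 v 10 with a true d of 0.5 and the rule d ≥ 0.5, the mean retained d is 0.83.

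**4. The protocol's own benchmark as go rule.** Suppose expected effects means an observed between-group difference of at least 5 points, and the true difference is exactly 5. For SDs of 5–12 at 20 v 10 and 20 v 20, the mean retained difference is 6.3–8.7 points, mean true power is 43–63%, and half of such pilots miss the trigger although the effect is real.

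**5. The alternative.** With the target fixed at 5 points, n per arm = 15.70 × SD²/25: 16 at SD 5, 41 at SD 8, 63 at SD 10 and 91 at SD 12. Only the SD then comes from the pilot, and it is much better determined: with 37 df its 95% limits are 0.82 to 1.29 times the estimate. Using the pilot SD as it stands gives average power of 78–80% for 5 points; using its one-sided 80% upper limit gives 86–87%. That limit is √(df/χ²₀.₂₀) times the estimate: 1.14 at 27 df, 1.12 at 37 df and 1.09 at 57 df.

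**The case against.** The strongest reply is that the protocol never says the observed point estimate will be the planning difference. It speaks of utilising data and informing a calculation, and Statistical methods promises a cautious reading. This stands as far as certainty goes. But the Abstract and Secondary objective both name effect size as an input, no shrinkage or confidence limit is described, and caution in interpreting the pilot does not lift the Discussion's condition.

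A second reply is that progression already rests on feasibility under Primary objective. That is correct. It makes the Discussion sentence inconsistent with the protocol's own rule, and it makes the repair easier.

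Third, the loss of power depends on an undefined trigger and an unknown true effect. This also stands. A reader might infer that the RCT is bound to be badly underpowered, and the documents do not support that: with a true d of 0.8 and a lenient trigger, mean power is about 75–77%. A reader might also infer that an unfavourable pilot would end development, but no section says what follows such a result.

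Fourth, the 5 points can be read as a within-person change or as a between-group difference, and they cover UPDRS-III only. That is fair, and the fix has to deal with it.

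**Conclusion.** The concern holds as a likelihood. Both elements are in the text: effect size as a planning input, and a condition on seeing favourable results. Direction and mechanism are secure, since mean true power fell below the nominal level in every scenario run. The size is not fixed by the protocol. Under the stated assumptions mean true power is about 23–65% at a true d of 0.3, 46–73% at 0.5 and 68–77% at 0.8, against a nominal 80%. The RCT is therefore likely to be underpowered, often severely, though not inevitably so. The consequence falls on a later trial that is not yet designed, and the conduct of this pilot is unaffected. The change is worth making because it protects the stated secondary objective at almost no cost.

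**What to change.** - In the Discussion, delete the opening condition about observing expected effects, and let progression follow the recruitment and usability criteria in Primary objective.
- In the Abstract and Secondary objective, state that the pilot supplies the SD, the baseline/follow-up correlation, attrition and data loss. Report pilot effects only as estimates with 95% CIs.
- State that the RCT will be powered on a prespecified relevant difference whatever effect the pilot shows. For UPDRS-III this can be the protocol's own 5 points, once Secondary objective makes clear that they are a between-group difference. For the kinematic and finger-tapping outcomes no relevant difference is given, and one must be set separately.
- Preferably plan on an upper confidence limit for the SD, about 1.09–1.14 times the estimate at 57 down to 27 df. The exact limit, and whether to plan on a baseline-adjusted model, are matters of preference.

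Cost: wording only, with no change to the pilot's conduct. The RCT may come out larger: inflating the SD by 1.12 raises n by 1.12² = 1.25, about 25%.
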